### Definitions

#### Heart Failure

Heart failure is defined as a “clinical syndrome consisting of cardinal symptoms (eg, breathlessness, ankle swelling, and fatigue) that may be accompanied by signs (eg, elevated jugular venous pressure, pulmonary crackles, and peripheral edema). It is due to a structural and/or functional abnormality of the heart that results in elevated intracardiac pressures and/or inadequate cardiac output at rest and/or during exercise” [7].

#### Reduced Left Ventricular Ejection Fraction

Reduced left ventricular ejection fraction is defined as an ejection fraction ≤40%, that is, those with a significant reduction in left ventricular systolic function [8].

## Methods

### Proposed Novel and Rapid Sequencing

The proposed algorithm for initiation of anti–heart failure therapy comprises of 3 steps once clinical euvolemia has been achieved with diuresis [2].

Step 1 is the concurrent initiation of treatment with a β-blocker and an SGLT2i. β-Blockers are pertinent in the treatment of HFrEF, especially in the context of reducing sudden cardiac death. Evidence has demonstrated reduced hospitalization for heart failure with the use of SGLT2is. The early diuretic effect of SGLT2is may attenuate the early risk of worsening heart failure when β-blockers are initiated [2].

Step 2 comprises of the addition of an ARNI (sacubitril and valsartan) within 1-2 weeks of step 1. The presence of hypotension (systolic blood pressure <100 mm Hg) warrants evaluation of blood response with an angiotensin receptor blocker before switching to an ARNI [2].

Step 3 is the addition of an MRA, within 1-2 weeks of step 2, depending on the serum potassium and the presence and degree of renal impairment. ARNIs and SGLT2i may improve renal function and potassium homeostasis, thereby permitting the use of MRAs. In patients with hypotension, MRAs may be used as step 2 [2].

The above algorithm represents a generic approach and may be individualized to specific scenarios. Patients with decompensated heart failure are a subgroup that require greater caution when initiating anti–heart failure therapy. β-Blocker therapy should only be initiated in the hospital after discontinuation of intravenous therapy for several days and the patient is clinically euvolemic, defined as the absence of rales and ascites and the presence of minimal peripheral edema [2].

In the appropriate patient, treatment with all 4 foundational treatments may be achieved within 4 weeks, with subsequent dose up-titration. This strategy increases the probability that highly effective therapies will be implemented in a manner that reduces mortality and hospitalizations and enhances the tolerability of subsequently administered treatments [1]. Figure 1 shows the proposed study flow diagram, which contains the novel and conventional sequencing approaches. A key difference is the rate at which therapies are added, with the novel sequence arm having patients on all the efficacious therapies initiated within 4 weeks.

**Figure 1 figure1:**
[figure not shown]
Study flow diagram. ACE: angiotensin-converting enzyme; ARB: angiotensin receptor blockers; ARNI: angiotensin receptor-neprilysin inhibitors; HCP: health care professional; MRA: mineralocorticoid receptor antagonists; SGLT2i: sodium/glucose cotransporter 2 inhibitors.

#### Study Design

This is a prospective, double-arm, randomized, assessor-blinded, and pragmatic clinical trial. The study will take place at a single site, that is, Tygerberg Hospital, Western Cape, South Africa.

#### Selection of Patients

Study participants will be adults with idiopathic dilated cardiomyopathy who consent to participate in the study. Patients will be free to withdraw at any time. The recruitment period will be 1 year.

Study participants will be randomized to the study arms by using a computer-generated randomization sequence.

Inclusion, exclusion, and withdrawal criteria are listed in Textbox 1.

Selection criteria (inclusion, exclusion, and withdrawal criteria).
**Inclusion criteria**
All patients aged <18 or >50 years who fulfill the clinical criteria for idiopathic dilated cardiomyopathy with reduced ejection fractionNew York Heart Association Functional class II-IV

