**Methods:**

This is a single-center, randomized controlled, double-arm, assessor-blinded, active control, and pragmatic clinical trial. Adults with stable heart failure with reduced ejection fraction and idiopathic dilated cardiomyopathy will be randomized to conventional sequencing (the control arm; over 6 months) of anti–heart failure therapies, and a second arm will receive rapid sequencing (over 4 weeks). Study participants will be followed for 5 years to assess the safety, efficacy, and tolerability of the 2 types of sequencing. Posttrial access and care will be provided to all study participants throughout their lifespan.

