## Discussion

### Principal Findings

This study aims to determine if rapid sequencing of anti–heart failure drugs with proven morbidity and mortality benefits would be superior to slower titration of these therapies.

We chose a composite end point to reduce the sample size, as a larger sample size would result in greater costs and reduce the feasibility of the study. Given the high mortality and frequent hospitalizations for heart failure, we included both events in the combined primary efficacy endpoint.

Intuitively, it makes sense to ensure that the most efficacious heart failure therapies are initiated as soon as possible. Given that the therapies have varied modes of action, we hypothesize that if they are started together as soon as possible, they would have greater benefits than starting them later. Combination therapies are likely to target different pathophysiological aspects of heart failure and thus improve clinical outcomes. Issues with rapid initiation may potentially include hypotension and other adverse effects. We will guard against hypotensive events by starting with the lowest possible dose and stopping the drug if the patient becomes hemodynamically unstable. Furthermore, study participants are required to be euvolemic before rapid sequencing so that we do not worsen patients’ heart failure and thus limit hemodynamic instability and decompensated heart failure. It is a standard clinical practice to ensure euvolemia before titration of anti–heart failure therapies. Euvolemia is usually achieved by loop diuretics [8].

We chose a relatively young group of patients so that underlying issues such as ischemic heart disease are less probable and would not serve as confounders. Furthermore, this group of patients may benefit from the increased life expectancy as compared with the older group.

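### The age limits are inverted in both the inclusion and the exclusion list: as written nobody can be enrolled, and the evidently intended adults aged 18 to 50 are shut out

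*Protocol article*

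**What the plan says.** The protocol article fixes the age limits in Textbox 1 under Selection of Patients. The inclusion list opens with "All patients aged <18 or >50 years who fulfill the clinical criteria for idiopathic dilated cardiomyopathy" and a reduced ejection fraction. The exclusion list opens with the mirror-image rule: anyone over 18 or under 50 is out.

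Elsewhere the article describes a different population:

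- **Abstract, Methods:** "Adults with stable heart failure with reduced ejection fraction and idiopathic dilated cardiomyopathy will be randomized to conventional sequencing".
- **Selection of Patients, just above the textbox:** "Study participants will be adults with idiopathic dilated cardiomyopathy who consent to participate in the study".
- **Discussion, Principal Findings:** "We chose a relatively young group of patients so that underlying issues such as ischemic heart disease are less probable". The next sentence adds that "this group of patients may benefit from the increased life expectancy as compared with the older group".
- **Rationale:** the case for the trial rests on a growing number of young people with this cardiomyopathy who are poorly treated and unlikely to receive a transplant.

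No section states a range of 18 to 50 outright.

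**The concern.** Age eligibility decides who is screened, who is asked for consent and to whom the result applies. Here both operative lists point the wrong way. The inclusion rule selects the two groups the text says the trial is not about, and the exclusion rule removes the group it is about.

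Three things are at stake:

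- **Enrolment.** Applied literally, the two lists leave no one to randomize, against a planned 584.
- **Population.** If staff apply only the inclusion line, or soften the exclusion line, the trial takes minors and people over 50. The second group is the one in which the Discussion implies ischemic heart disease is more likely.
- **Assumptions.** The sample size assumes a primary-outcome incidence of at least 50% over 5 years in the conventional arm. Under the lists as written, that assumption would be applied to a population other than the one described. Consent is also framed around adults who agree to take part, which does not fit a rule that admits children.

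**Working it through.** There is no stated figure to reproduce; the check is one of logic. Let *a* be age in years.

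**Inputs, from Textbox 1**

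- Inclusion rule, I: *a* < 18 or *a* > 50.
- Exclusion rule, E: *a* > 18 or *a* < 50.
- A patient is eligible on age if I is true and E is false.

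**Step 1: the lists as written.** E is false only if *a* ≤ 18 and *a* ≥ 50 together, which is impossible. E is therefore true at every age, and the eligible set is empty whatever I says.

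**Step 2: a generous reading.** Suppose the exclusion was meant as *a* > 18 **and** *a* < 50. Then the exclusion removes only ages strictly between 18 and 50. Those who pass both rules are under 18 or over 50. Ages exactly 18 and exactly 50 escape the exclusion but fail the inclusion.

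**Step 3: the rules exchanged.** Include 18 ≤ *a* ≤ 50; exclude *a* < 18 or *a* > 50. The two lists are now complements of each other, and the eligible ages are 18 to 50.

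| Age | Meets inclusion as written | Excluded, literal *or* | Eligible, literal | Excluded, *and* reading | Eligible, *and* reading | Eligible, rules exchanged |
|---|---|---|---|---|---|---|
| Under 18 | yes | yes | no | no | yes | no |
| Exactly 18 | no | yes | no | no | no | yes |
| Between 18 and 50 | no | yes | no | yes | no | yes |
| Exactly 50 | no | yes | no | no | no | yes |
| Over 50 | yes | yes | no | no | yes | no |

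Applying each rule to ages 0 to 120 in half-year steps gave the same three results: no eligible age on the literal reading, none from 18 to 50 on the *and* reading, and 18 to 50 once the rules are exchanged.

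**Step 4: comparison with the text.** Only the last column agrees with the description of participants as adults and with the stated preference for younger patients. The *and* reading conflicts with the first because it admits minors. It conflicts with the second because the only adults it admits are over 50.

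**Step 5: is it a text-conversion fault?** The other inequality signs in the same exclusion list make sense as exclusions: systolic pressure ≥180 or <100 mm Hg, estimated filtration rate <30, potassium >5.4 mmol/L, events ≤90 days before visit 1. Only the age signs conflict with the text, and they do so consistently in both lists. That points to the two age rules having been transposed in the source.

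**The case against.** The best reply is that this is a slip anyone can see through. The intent can be recovered from the abstract, the Selection of Patients section and the Discussion, and a sensible investigator would screen adults of 18 to 50. Recruitment has not begun, so nobody has been harmed, and the full protocol may word it correctly. That lowers the practical harm so far. It does not rescue the text, because an eligibility list should not depend on the reader guessing that it means its opposite.

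Four narrower points have some force:

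- **The empty set depends on a strict *or*.** True. The more robust statement is that ages 18 to 50 are shut out on either reading.
- **18 to 50 is an inference.** Also true. It is a strong one: two cut-offs, plus a description of participants as adults and relatively young.
- **Other safeguards remain.** Inclusion still requires criteria for idiopathic dilated cardiomyopathy. Recent acute coronary syndrome and bypass surgery are excluded, as are patients unable or unwilling to consent. These would limit ischemic disease and the enrolment of minors. They do not replace the age restriction that the Discussion relies on.
- **The effect on the event rate is not quantified.** Correct. The 50% assumption is not tied to age and the article gives no rates by age, so this is a risk without a size.

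**Conclusion.** The concern holds. As written, the two lists together admit no one, and even on the kindest reading of the exclusion rule they admit no one aged 18 to 50. This is an internal contradiction in the operative eligibility criteria and must be corrected before the protocol is used.

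The conclusion that ages 18 to 50 are shut out needs no assumption. The conclusion that nobody is eligible rests on reading *or* literally. That the intended range is 18 to 50 is inferred from the rest of the article. The possible consequences for event rate and confounding are real in direction but cannot be sized from the document.

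**What to change.** Exchange the two age rules in Textbox 1 and write the bounds explicitly:

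- **Inclusion:** aged at least 18 and at most 50 years.
- **Exclusion:** aged under 18 or over 50 years.

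Moving the two lines across unchanged is not enough. The inclusion line would then read as over 18 *or* under 50, which everyone meets, so it needs *and* between its two bounds. Including exactly 18 and exactly 50 follows from using strict inequalities in the exclusion; the sponsor should confirm the range and both boundaries. Carry the same limits into the screening form.

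The cost is two lines of wording. The Results section says the ethics application will follow once funding is obtained, so the correction can be made before submission.

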**Exclusion criteria**
Aged >18 years or <50 yearsUnable or unwilling to provide informed consent to undergo any of the recommended investigations or to participate in the studyAcute coronary syndrome, bypass graft surgery or other major cardiac surgery, stroke, or transient ischemic attack ≤90 days from visit 1Acute decompensated heart failureSystolic blood pressure ≥180 mm Hg or <100 mm HgEstimated glomerular filtration rate <30 mL/min/1.73 m^2^Serum potassium level >5.4 mmol/LHistory of angioedema
**Withdrawal criteria**
Patient decision to leave the studyAdverse drug reactions

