#### Secondary Objectives

Secondary end points include death from cardiovascular causes (eg, cardiogenic shock, myocardial infarction, tachycardia, or brady-arrythmia), improvement in the 6-minute walk test, improvement in the New York Heart Association functional class, improvement in symptoms as per the Kansas City Cardiomyopathy Questionnaire, trans-esophageal echo-determined ejection fraction (chamber dilatation, left ventricular systolic function, global longitudinal strain, and speckle tracking), and N-terminal prohormone of brain natriuretic peptide levels. Adverse drug reactions will also be collected and analyzed.

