### Statistical Considerations

#### Sample Size

We determined that a target number of 248 primary outcome events would provide a power of 80% to detect a 30% lower relative risk of the primary outcome in the novel sequencing arm than in the conventional sequencing arm at a 2-sided α level of .05. Assuming an incidence of the primary outcome of at least 50% over 5 years in the conventional sequencing arm and a dropout of 10% per arm, we established a planned enrolment of 584 patients (292 per study arm).

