#### Analysis Population

The analysis population will include all study participants included in the study. This is an intention-to-treat analysis and even participants who have withdrawn, or dropped out, from the study after randomization will have their data analyzed.

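### Textbox 1 makes an adverse drug reaction a criterion for leaving the study, which may undermine the promised intention-to-treat analysis unless outcomes are still followed to 5 years

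*Protocol article*

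**What the plan says.** Four places in the protocol article bear on this.

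- **Textbox 1, Withdrawal criteria.** The whole list is "Patient decision to leave the studyAdverse drug reactions" (two entries, run together in the text). The second entry has no severity threshold and does not say whether the patient leaves a drug or the trial.
- **Analysis Population.** "This is an intention-to-treat analysis and even participants who have withdrawn, or dropped out, from the study after randomization will have their data analyzed". Withdrawal here means withdrawal from the study.
- **Discussion, Principal Findings.** "Issues with rapid initiation may potentially include hypotension and other adverse effects". The stated safeguards include "stopping the drug if the patient becomes hemodynamically unstable"; leaving the study is not mentioned.
- **Abstract, Methods, and Secondary Objectives.** "Study participants will be followed for 5 years to assess the safety, efficacy, and tolerability of the 2 types of sequencing", and "Adverse drug reactions will also be collected and analyzed".

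The Sample Size section assumes the same 10% dropout in each arm. Table 1 names Cox proportional hazards regression for both components of the primary end point. No passage gives a reaction rate for either arm. None says that outcomes are still collected after withdrawal, and none says that collection stops.

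**The concern.** An adverse drug reaction is a consequence of the strategies under comparison, and it is one of the trial's own outcomes. Making it a ground for leaving the study lets retention depend on treatment. Intention-to-treat needs outcomes on everyone randomized, not only a place in the analysis set. A patient who leaves at month 2 and whose data to month 2 are analyzed contributes two months of follow-up and is then censored.

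The Cox model treats that censoring as unrelated to later risk. If patients who react have a different risk of death or heart failure hospitalization, and the arms lose different numbers of them, the hazard ratio is biased. Enrolling more patients does not remove this. Later harm in the patients who tolerated treatment least would also go unseen, in a trial meant to assess safety and tolerability.

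**Working it through.** **1. The plan's own figures.** With a hazard ratio of 0.70, two-sided alpha 0.05 and 80% power, the events needed are 4 × (1.960 + 0.842)² / (ln 0.70)² = 246.8. The stated 248 gives 80.2% power. For enrolment, take exponential event times (control hazard λc = ln 2 / 5 = 0.1386 per year; rapid hazard 0.70 × λc) and 10% dropout over 5 years as gradual censoring at rate d = −ln(0.9)/5. The event probability is λ/(λ+d) × [1 − exp(−5(λ+d))], which is 0.477 in the control arm, 0.366 in the rapid arm and 0.422 on average. Then 246.8 / 0.422 ≈ 585, against the stated 584. (248 / 0.425, using risks of 50% and 35% with no dropout, also gives 584, so the method used cannot be determined.) The sample size is not in error on this point.

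**2. Bias if follow-up ends at withdrawal.** From the documents: 50% control risk at 5 years, 5 years of follow-up, target ratio 0.70. Everything else is assumed:

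- a share q of each arm is reaction-prone, with f times the hazard of the other patients;
- a fraction w of the arm withdraws, all from that share, uniformly over the first 6 months;
- q equals the larger of the two withdrawal rates;
- everyone else is followed for 5 years.

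Holding the mean hazard at 0.1386, the other patients have λ = 0.1386 / (1 − q + qf) and the prone have f times that. Events per patient are 1 − exp(−5λ) if followed, and 1 − [1 − exp(−0.5λ)] / (0.5λ) if withdrawn. Person-years are events divided by λ.

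Example with no true effect, f = 2, q = 0.15, so λ = 0.1205 and 0.2411:

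| Group | Events per patient | Years per patient |
|---|---|---|
| Not prone | 0.4527 | 3.755 |
| Prone, followed | 0.7004 | 2.905 |
| Prone, withdrawn | 0.0579 | 0.240 |

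- Control, 5% withdrawn: events 0.85 × 0.4527 + 0.10 × 0.7004 + 0.05 × 0.0579 = 0.458; years 0.85 × 3.755 + 0.10 × 2.905 + 0.05 × 0.240 = 3.495; rate 0.1310.
- Rapid, 15% withdrawn: events 0.85 × 0.4527 + 0.15 × 0.0579 = 0.393; years 0.85 × 3.755 + 0.15 × 0.240 = 3.228; rate 0.1219.
- Ratio 0.1219 / 0.1310 = 0.93, where the truth is 1.

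The same formulas give:

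| Withdrawn, control vs rapid | True ratio | f = 1 | f = 1.5 | f = 2 | f = 3 |
|---|---|---|---|---|---|
| 5% vs 5% | 1.00 | 1.000 | 1.000 | 1.000 | 1.000 |
| 5% vs 10% | 1.00 | 1.000 | 0.980 | 0.965 | 0.944 |
| 5% vs 15% | 1.00 | 1.000 | 0.960 | 0.931 | 0.890 |
| 5% vs 10% | 0.70 | 0.700 | 0.685 | 0.675 | 0.660 |
| 5% vs 15% | 0.70 | 0.700 | 0.671 | 0.651 | 0.623 |

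These are ratios of event rates. A Cox fit to data simulated from the same model agrees closely. Bias needs both unequal loss and a difference in risk; with either absent it vanishes. The setup leans toward larger bias, since every withdrawn patient is high-risk and all prone patients leave the arm with the higher rate.

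**3. Power.** Under the planned dropout, events are 292 × 0.477 + 292 × 0.366 ≈ 246, with power Φ(√246 × 0.357/2 − 1.96) = 79.9%. An extra early loss of 5%, 10% or 20% in the rapid arm alone leaves about 241, 236 or 225 events, and 79%, 78% or 76% power. If leavers are also high-risk, more events go: in the last cell of the table above, about 207, or 73% by event count. In that case the ratio itself is displaced, so bias is the main problem.

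**The case against.** The strongest reply is that the text says less than a critical reader may take from it. Textbox 1 is a bare two-item list in a condensed article. The Abstract commits to 5 years of follow-up, and the Analysis Population section keeps withdrawn participants in the analysis. The Discussion describes stopping a drug, so the authors may mean no more than that. Both arms receive the same four drug classes, adverse effects of rapid initiation are mentioned only as a possibility, and the Discussion expects limited problems. Nothing in the documents shows that patients who react are at higher risk.

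Most of this stands as a limit on the claim. A reader might infer that follow-up ends selectively in the rapid arm and that intention-to-treat is thereby defeated. The documents do not support that: they do not say that collection stops, they give no reaction rates by arm, and the higher risk of reacting patients is an assumption. Nor do they say whether withdrawals for reactions fall inside or outside the 10% dropout.

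The criterion itself does not go away. It is stated, not left to a fuller document, and it sits beside the patient's decision to leave the study. The article elsewhere describes withdrawal as being from the study. Keeping withdrawn patients in the analysis set supplies no outcomes that were never collected. Even on the kindest reading, the three places leave it unclear who is followed for the primary end point.

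**Conclusion.** The point holds in this form: the withdrawal criterion merges stopping a drug with leaving the trial and, followed as written, may undermine the intention-to-treat analysis of the primary end point. That rests on reading study withdrawal as the end of outcome collection. The direction of bias is conditional. It favors rapid sequencing only if that arm loses more patients and those patients are at higher risk; if the control arm lost more of them, it would go the other way. On the assumptions above, a true ratio of 1 appears as about 0.98 to 0.89, and a true 0.70 as about 0.69 to 0.62. With equal risk there is no bias. Power is a secondary matter, and the stated 248 events and 584 patients are unaffected. It should be corrected before the trial starts.

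**What to change.** Reconcile Textbox 1, the Analysis Population section and the Discussion:

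- Remove adverse drug reactions from the criteria for leaving the study.
- State that a participant who stops a study drug for any reason stays in the trial under the randomized allocation. That participant is followed to 5 years for death and heart failure hospitalization, through clinic visits, hospital records or vital status, unless consent to follow-up is withdrawn.
- Record stopping a drug separately from withdrawing consent to follow-up.

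When a drug is stopped or changed remains with the investigators; nothing here bears on that.

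The cost is one line in Textbox 1, a sentence in the Analysis Population section, a change to the consent text and a small effort to follow records. The trial runs at one hospital, whose cardiology clinic is to provide lifelong post-trial care, so the follow-up is practical. Funding and ethical approval were still outstanding when the article was written, so the change can be made before anyone is enrolled.
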